### Data management and analysis

Data collected from each participant is recorded on paper-based case report forms (CRFs) in black ballpoint pen. The principal investigator will ensure that the data in the CRFs are accurate, complete, and legible. Data from the case record forms is entered by a data clerk into computers as they accrue using the MS Access program. The data is verified by comparing it with the CRFs. Missing data is imputed as either treatment success or treatment failure (assuming the same infection intensities before and after treatment). Validated data is transferred to SPSS version 20 and STATA version 12 for statistical analyses. The CRFs and the electronic data will be kept for 5 years after the primary manuscripts are published.

Data is analyzed using SPSS for Windows version 20 (SPSS Inc., Chicago, IL) and STATA version 12.0 (StataCorp., College Station, TX, USA) packages. A two-sided *p*-value less than 0.05 is considered statistically significant for all tests.

Demographic and other baseline characteristics are compared to check for imbalances between the study groups. These measures will be tabulated from the intent-to-treat population. Significance tests are not performed to compare the differences between study groups at baseline. Where imbalances are suspected, additional analyses are performed to adjust for these variables.

To determine efficacy, both the per-protocol and intention-to-treat analyses are done, but the per-protocol analysis is the main approach. The primary efficacy outcome is the cure rate, defined as the proportion of children infected with *S. mansoni* at enrollment but not excreting eggs by week 6 after taking the study treatment. In the computation of the cure rate, children randomized to the PZQ alone study arm are considered the control group. Cure rates are compared between the treatment groups using Pearson’s chi-square test for contingency tables (in a per-protocol analysis) and summarized as absolute risk differences with 95% confidence intervals (CI). The per-protocol population is defined to include all participants who were randomized and who completed the study procedures to week 6 or 12. The primary hypothesis for non-inferiority is assessed by considering the lower limit of the 95% CI for the risk difference. Non-inferiority is concluded if the lower bound of the 95%CI from the risk difference does not exceed the non-inferiority margin of − 10.

The cumulative cure rate at week 12 is assessed by calculating a two-sided difference in proportions of cured children from each PZQ plus ACT arm compared with the PZQ alone arm. Arithmetic mean (AM) egg counts are computed for all non-cured participants. The egg reduction rate is computed as (1 − (AM EPG after treatment/AM EPG before treatment)) × 100. The ERR is expressed as a percentage. Re-infection rate is the proportion of children who test negative for *S. mansoni* at week 6 but test positive at week 12 follow-up. Changes in continuous variables over time are assessed using analysis of variance (ANOVA). The least significant difference will be used to assess post hoc pair-wise comparisons between the group means. Logistic regression will be used for analyses adjusted for the treatment received.

For the primary safety analysis, the frequency and pattern of adverse events are computed by patient counts and percentages in each of the five treatment groups. Adverse events are computed for all participants who received at least one dose of the study drug (intention-to-treat population).

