### Outcomes

The primary efficacy outcomes are as follows:Cure rate at week 6 after starting study treatments, as assessed by microscopy. The cure rate on each PZQ plus ACT arm is compared with that on the PZQ alone arm.The number of participants with drug-related adverse events in the first 24 h after study treatment.

The secondary outcomes are as follows:Cumulative cure rate at week 12 after enrollment, as assessed by microscopy. The cure rate on each PZQ plus ACT arm is compared with that on the PZQ alone arm.Egg reduction rate at weeks 6 and 12 after starting treatment, as assessed by microscopy and intensity reduction rate, comparing each PZQ plus ACT with PZQ alone arm.The prevalence of re-infection at 12 after starting treatment, as assessed as the number of children who were cured at week 6 follow-up but positive for *S. mansoni* at the week 12 follow-up, compared each PZQ plus ACT arms to the PZQ alone arm.

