#### Withdrawal

Participation is voluntary, and participants can withdraw from the study at any time and for any reason without consequences. Participants will be withdrawn from the study due to repeated vomiting or occurrence of SAE. Children with SAEs are followed up until the end of 6 weeks after the last treatment dose. Participants withdrawn from the study due to medical reasons are referred to adequate health facilities for further care. Unless consent is withdrawn, efforts are made to assess these children at the week 6 follow-up schedule.

Valid reasons for study discontinuation include completion of the scheduled follow-up period and exclusion from follow-up. Randomized participants who miss one or more scheduled follow-up visits remain in the study and are followed up as planned. Loss to follow-up is expected to be minimal because all the participant-related study procedures are completed at school and, if necessary, at home. In the unlikely event that a study participant moves away from the study area during the study period, they are considered lost to follow-up and are not included in the efficacy analysis. However, data collected up to the time of withdrawal will remain in the study and be used for analysis of whether or not the participant continues with the follow-up visits. Participants who have been withdrawn from the study are administered a standard dose of praziquantel after the final study visit. No additional participants are recruited to replace those who have withdrawn.

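### The failure branch of the missing-data rule carries the baseline egg count forward; wherever it is used for the egg reduction rate, it lowers the rate in proportion to loss and adds noise

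*Protocol article*

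**What the plan says.** The missing-data rule in Data management and analysis reads: "Missing data is imputed as either treatment success or treatment failure (assuming the same infection intensities before and after treatment"). It is not limited to any outcome, visit or analysis set. Infection intensity in this article is eggs per gram (EPG), as set out under Parasitological monitoring of response to treatment, so the bracket is a rule about egg counts.

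The secondary outcomes include "Egg reduction rate at weeks 6 and 12 after starting treatment", with each combination arm compared with praziquantel alone. The rate is one minus the ratio "AM EPG after treatment/AM EPG before treatment", as a percentage. The sentence just before the formula says: "Arithmetic mean (AM) egg counts are computed for all non-cured participants". No analysis set is named for this outcome.

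For efficacy in general, "both the per-protocol and intention-to-treat analyses are done, but the per-protocol analysis is the main approach". The per-protocol population is "all participants who were randomized and who completed the study procedures to week 6 or 12". Under Withdrawal, children who move out of the area are handled differently from the imputation rule: "they are considered lost to follow-up and are not included in the efficacy analysis". The same section keeps children who miss visits in the study.

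**The concern.** The bracket can describe only a child imputed as a failure, because an imputed success would have zero EPG. For a failure it means that the post-treatment count equals the pre-treatment count, so no treatment effect is assumed in that child.

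The egg reduction rate is a ratio of arithmetic means. Most treated children are expected to be at or near zero, so a few untreated-level counts can make up a large part of the post-treatment mean. The reported rate then reflects completeness of follow-up as well as drug effect. If follow-up differs between arms, two regimens with the same effect on eggs would show different rates.

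The article does not say which branch serves which child, outcome or analysis set, or that the two are meant as bounds. The data analysts are not blinded (Randomization and blinding), which is a further reason to fix the choice in advance.

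**Working it through.** **Inputs from the article.** Planned loss to follow-up is 5%, and the praziquantel cure rate is 72% (Sample size). The formula and the averaging over non-cured children come from Data management and analysis. The loss allowance reproduces: 102 / 0.95 = 107.4, rounded up to 108 per arm, and 5 × 108 = 540.

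**Assumptions.** The article states no egg reduction rate and no loss by arm. The true rate R, the 2% and 8% losses, and the independence of loss from baseline count are therefore assumptions. Let f be the share followed up, c the cure rate, and set the mean baseline count to 1.

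**1. Failure fill, means over all randomized children.**
Rate = 1 − [f(1 − R) + (1 − f)] = f × R.
At f = 0.95, true rates of 80, 90, 95 and 99% become 76.0, 85.5, 90.25 and 94.05%.
At R = 95%, the carried-forward counts supply 0.05 of a post-treatment total of 0.95 × 0.05 + 0.05 = 0.0975, or about half.

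**2. Failure fill, means over non-cured children.** Imputed failures join the non-cured group, and the rate among the non-cured is multiplied by f(1 − c) / [f(1 − c) + (1 − f)].
At f = 0.95 and c = 0.72: 0.266 / (0.266 + 0.05) = 0.842, so an assumed 80% becomes 67.3%.
If cured and non-cured children have the same mean baseline count, 80% among the non-cured with 72% cured is 1 − 0.28 × 0.20 = 94.4% over all children. Steps 1 and 2 therefore describe much the same drug effect.

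**3. Success fill (zero EPG), means over all children.**
Rate = 1 − f(1 − R). At R = 95% and f = 0.95 this is 95.25%.

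**4. Measured counts only.** The rate stays at R whatever the loss, if loss is unrelated to outcome.

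**5. Unequal loss, same drug effect (assumed 2% versus 8%).**

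| Method | 2% loss | 8% loss | False gap |
|---|---|---|---|
| Failure fill, all children, R = 95% | 93.1% | 87.4% | 5.7 points |
| Failure fill, non-cured only, 80% | 74.6% | 61.0% | about 13.5 points |
| Success fill, all children, R = 95% | 95.1% | 95.4% | 0.3 points, opposite direction |
| Measured counts only, R = 95% | 95% | 95% | 0 |

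The first gap is 4.8 points at R = 80% and 5.9 points at R = 99%.

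**6. Loss related to baseline count.** If lost children have k times the mean baseline count, the failure fill over all children gives R × [1 − (1 − f)k]. At R = 95% and f = 0.95 this is 92.6% for k = 0.5 and 85.5% for k = 2.

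**7. Noise.** Simulated trials with 108 per arm used assumed negative binomial counts (dispersion 0.5, mean about 200 EPG) and 72% cured. With equal 5% loss in both arms, the standard deviation of the between-arm difference was about 5.1 points under the failure fill over all children, against 1.9 points with measured counts only. The loss of precision therefore does not need unequal loss.

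**8. Where the fill can enter.** The intention-to-treat analysis includes children without a follow-up count. In the per-protocol set, the condition of completing to week 6 or 12 can admit a child seen at week 6 but not at week 12. The rule would then replace that child's week-12 count with the baseline value, even if the week-6 count was zero.

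**The case against.** The strongest reply is that the rule offers two fills, and that a success/failure pair reads naturally as best-case and worst-case bounds. The main efficacy approach is per-protocol among completers, and children who move away are left out of the efficacy analysis. On that reading the main egg reduction rate already rests mostly on measured counts. A condensed article may also leave the allocation of fills to a fuller document.

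Much of this stands. A reader might infer that every missing count takes the baseline value and that the egg reduction rate then largely measures follow-up. The documents do not support that: one branch is a success fill that barely moves the rate, and the main week-6 estimate is largely unaffected. Nor is the reported rate simply the true rate times the share followed up. That identity needs means over all children, whereas the article averages over the non-cured, where the factor also depends on the cure rate.

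A reader might also infer that the combination arms will lose more children, because dosing lasts three days and repeated vomiting or a serious adverse event leads to withdrawal. This is plausible but not documented. The article expects minimal loss, provides home visits for non-attenders, and tries to assess withdrawn children at week 6 unless consent is withdrawn.

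The reply does not remove the problem. Intention-to-treat efficacy is also planned, the per-protocol wording can leave week-12 counts missing, no analysis set is named for the egg reduction rate, and nothing labels the fills as bounds. The rule is stated and unrestricted, and it sits badly with the exclusion under Withdrawal.

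**Conclusion.** The point holds in a limited form and concerns a secondary outcome. The bias arises only where the failure branch is applied. At the planned 5% loss it costs 4 to 5 points on assumed true rates of 80% to 99% when means cover all children, and about 13 points on an assumed 80% under non-cured averaging with 72% cured. These figures assume loss unrelated to baseline count; step 6 shows how they move otherwise. Any false difference between arms depends on a difference in loss that the documents do not give, so the 5.7 points is an illustration and not a forecast. The added noise rests on the simulated count distribution but arises even with equal loss. The plan should be changed on this point.

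**What to change.** 1. Compute the main egg reduction rate from children with a measured count at baseline and at the visit concerned, or by multiple imputation from arm, baseline count and the other follow-up count. Name the analysis set for each visit.
2. Keep the success and failure fills only as labelled best-case and worst-case sensitivity analyses, and attach the same-intensity wording to failures alone.
3. Reconcile the imputation sentence with the exclusion of children who move away, and state whether a child seen only at week 6 belongs to the week-12 per-protocol set.

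The cost is a few sentences and one extra analysis run. The small downside is that the main figure assumes loss is unrelated to egg count given the data used; the two sensitivity analyses check how far the result depends on this.

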### Sample size

The sample size is calculated using the statistical test for proportions based on the hypothesis that combination therapy using praziquantel plus an artemisinin-based combination is not inferior to praziquantel alone in treating schistosomiasis. Assuming a cure rate of 72% with praziquantel based on longitudinal studies from western Kenya [29], a cure rate of 62% (maximum difference of 10%) is considered clinically acceptable for non-inferiority of praziquantel plus an ACT combination therapy. With this non-inferiority margin, a power of 80%, and a one-sided alpha value of 0.025, a sample size of 102 children is needed in each treatment arm. To account for a 5% loss to follow-up, the total number of children to be enrolled and randomized is 540 (108 in each study arm).

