#### Parasitological monitoring of response to treatment

All the laboratory tests are performed by the laboratory at the sub-county hospital, using standard techniques. To assess for the presence of *S. mansoni*, participants provided a fresh stool sample. Duplicate slides are prepared from the stool sample and examined under the microscope independently by two experienced laboratory technicians. The *S. mansoni* and soil-transmitted helminth eggs are quantified by use of the Kato-Katz fecal thick-smear technique, with a template containing about 41.7 mg of feces when filled. The number of *S. mansoni* eggs is counted per slide, and the mean of the two readings is multiplied by 24 to express them as eggs per gram (EPG) of feces. The intensity of infection is categorized according to the WHO classification as light (1–99 EPG), moderate (100–399 EPG), or heavy (≥ 400 EPG) [30]. As a quality control measure for interobserver variability, a third technician reads a random selection of 10% of slides, and all slides for which the initial readings vary by more than 20% between the two technicians.

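### The cure-rate comparison leaves baseline egg count unused and ties adjustment to an undefined imbalance trigger: a modest, avoidable loss of precision, not an invalid primary analysis

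*Protocol article*

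**What the plan says.** Only the protocol article is at hand. Under Data management and analysis, cure rates are compared by Pearson's "chi-square test for contingency tables (in a per-protocol analysis) and summarized as absolute risk differences" with 95% confidence intervals. Non-inferiority is read from the lower limit of that interval against a margin of -10. No covariate enters this comparison.

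The same section tabulates baseline characteristics in the intention-to-treat population, rules out significance tests on them, and then states: "Where imbalances are suspected, additional analyses are performed to adjust for these variables". It does not say which variables qualify, what size of imbalance counts, or who judges it. Randomization and blinding says that data analysts are not blinded.

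Baseline egg counts exist for all participants. A positive stool is an entry criterion, eggs are quantified by Kato-Katz, and "The intensity of infection is categorized according to the WHO classification as light", moderate or heavy. Egg counts before treatment are also needed for the egg reduction rate.

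The only regression model named for adjustment is this: "Logistic regression will be used for analyses adjusted for the treatment received". It names no baseline covariate.

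**The concern.** Two things are at stake.

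- **Precision.** If infection intensity at entry predicts clearance, an analysis that ignores it gives a wider interval than the same data could support. The documents do not state that heavier infections clear less often, so this is a plausible assumption and not a documented fact. It matters here because the expected half-width already exceeds the 10-point margin.
- **The rule for adjustment.** The protocol does more than leave a covariate list to an analysis plan. It states a rule that depends on the data: look at the baseline table, suspect an imbalance, then adjust. With no significance tests, no threshold and no list, the rule rests on judgement alone, and those who apply it know the arms. Under individual randomisation, observed imbalance is also a weak reason to adjust. The better reason is that a variable predicts the outcome, and that can be settled beforehand.

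**Working it through.** **Inputs from the Sample size section.** "Assuming a cure rate of 72% with praziquantel"; "a cure rate of 62% (maximum difference of 10%) is considered clinically acceptable"; "a power of 80%, and a one-sided alpha value of 0.025"; "a sample size of 102 children is needed in each treatment arm". No expected cure rate is given for the combinations, so equality at 72% is assumed below.

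**Step 1: the plan's own figure.** For a difference in proportions under true equality,

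n per arm = 2 × 0.72 × 0.28 × (1.96 + 0.8416)² / 0.10² = 0.4032 × 7.849 / 0.01 ≈ 316.5, so 317.

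The stated 102 is not reproduced. Values near it appear only if the combination cures about 79% (n = 100) or the margin is about 17.5 points (n = 104), and neither is stated. The dropout step does reproduce: 102 / 0.95 = 107.4, so 108, and 5 × 108 = 540.

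**Step 2: precision of the unadjusted analysis at 102 per arm.**

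- Standard error = √(0.4032 / 102) = 0.0629.
- Half-width = 1.96 × 0.0629 = 12.3 points.
- Power = Φ(0.10 / 0.0629 − 1.96) = Φ(−0.37) = 35.6%.

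**Step 3: gain if covariates explain a share R² of the variance in cure.** As an approximation, the variance of the risk difference is multiplied by (1 − R²). R² is assumed.

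| R² | Half-width (points) | Equivalent n per arm, 102/(1 − R²) |
|---|---|---|
| 0 | 12.3 | 102 |
| 0.05 | 12.0 | 107 |
| 0.10 | 11.7 | 113 |
| 0.15 | 11.4 | 120 |
| 0.20 | 11.0 | 128 |

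**Step 4: egg count alone.** Here R² is derived from a logistic model of cure on standardised log baseline egg count, with overall cure held at 72%. The odds ratio per SD is assumed.

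| Odds ratio per SD | R² | Half-width (points) | Power at 102 per arm | n per arm for 80% power |
|---|---|---|---|---|
| 1.0 | 0 | 12.3 | 35.6% | 317 |
| 0.8 | 0.010 | 12.3 | 35.9% | 314 |
| 0.67 | 0.031 | 12.1 | 36.5% | 307 |
| 0.5 | 0.084 | 11.8 | 38.3% | 290 |
| 0.4 | 0.134 | 11.5 | 40.1% | 275 |
| 0.33 | 0.179 | 11.2 | 41.9% | 260 |

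The largest gain is 41.9 − 35.6 = 6.3 power points. To reach 80% power with 102 per arm, R² would have to be 1 − 102/316.5 ≈ 0.68.

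**Step 5: does a free choice of covariates affect the error rate?** Trials were simulated at the non-inferiority boundary (72% against 62%, 102 per arm, five candidate covariates, 4,000 runs, two seeds). Two prognostic settings were used: odds ratio 0.67 for egg count with the rest null, and 0.5 with 0.8 for the rest. The adjusted fits were linear models with robust variance. One-sided error was:

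- 2.2% to 2.5% when the unadjusted analysis decides;
- 2.4% to 2.8% when pre-specified egg-count adjustment decides;
- 3.3% to 4.9% when the most favourable of all 32 covariate sets decides.

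The protocol describes the first of these. It does not describe the third.

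**The case against.** A reader might infer that the rule yields two competing primary answers, or that unblinded choice of covariates inflates the primary error rate. The text does not support this. The decision rests on the confidence interval of the pre-stated comparison, which is unadjusted, and the imbalance-driven work is called additional. The 3.3% to 4.9% error arises only if an additional analysis is promoted to decide the trial, which the protocol does not provide for.

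Four further objections have weight.

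- **Validity.** An unadjusted risk difference is valid under individual randomisation, and no stratification factor is described that the analysis omits. This stands. The per-protocol set adds a possible selection after randomisation, but that is a separate matter, and egg-count adjustment would address it only in part.
- **Size.** The prognostic strength is assumed and the gain is modest. With an observed difference of zero the lower limit would be about -12.3 unadjusted and -11.0 at R² of 20%, and both miss -10. This stands. The low power comes from the sample-size calculation and should not be counted again here.
- **What an analysis plan may hold.** A covariate list is commonly left to it, so the absence of a list is not a fault in itself. This also stands. The trigger, however, is written in the article and can be judged as written.
- **Timing.** Trial status puts the end of recruitment at 30 November 2022 and the trial in final follow-up. Changing the deciding estimator late, with unblinded analysts, could itself look post hoc. This limits the fix: the choice has to be recorded before analysis, and keeping the unadjusted difference as the deciding one is acceptable.

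**Conclusion.** The point holds as one of efficiency and pre-specification. The primary comparison ignores a baseline measurement that the trial already has, and the supporting adjusted analyses depend on an undefined trigger applied by unblinded analysts. The primary analysis remains valid, and its error rate is not shown to be inflated.

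If baseline covariates explain 0% to 20% of the variance in cure, the half-width at 102 per arm falls from 12.3 points to between 12.3 and 11.0. For egg count alone, with an odds ratio per SD from 1.0 to 0.33, power at true equality of 72% rises from 35.6% to between 35.6% and 41.9%. These ranges rest on assumed prognostic strength, equal cure in both arms and the (1 − R²) approximation. Over the whole range the half-width stays above the margin, so adjustment does not resolve the gap between 102 and 317 per arm.

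**What to change.** Before analysis begins:

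1. Pre-specify one adjusted estimate: the risk difference standardised from a logistic model with arm, log baseline eggs per gram and age, plus school if numbers per school allow. Give it a delta-method or bootstrap 95% CI, set against -10.
2. State in advance whether this estimate or the unadjusted difference decides non-inferiority, and report both.
3. Replace the imbalance trigger with this fixed covariate list.
4. Clarify what the logistic regression adjusted for treatment received is meant to estimate. No harm from it has been shown that would require deleting it.

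No new data are needed, since egg count, age and school are already recorded. The cost is a few lines of text and code, plus ethics approval if the change is made as a protocol amendment, which the Ethics approvals section requires.

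### Per-protocol is made the lead analysis for efficacy without limit, so it also leads the week-12 cure comparison, a difference test in which a completers-only lead can produce a false ACT benefit

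*Protocol article*

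**What the plan says.** All of this is in the protocol article, under Data management and analysis unless stated.

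- Lead analysis set, in a sentence on efficacy as a whole: "both the per-protocol and intention-to-treat analyses are done, but the per-protocol analysis is the main approach". The sentence names no time point and no type of test.
- Per-protocol set: "all participants who were randomized and who completed the study procedures to week 6 or 12". The mention of week 12 carries the set to the week-12 outcomes.
- Non-inferiority: the margin of 10 points is tied to the primary hypothesis only.
- Week-12 cure: "The cumulative cure rate at week 12 is assessed by calculating a two-sided difference in proportions of cured children from each PZQ plus ACT arm". The comparator is praziquantel alone, and no margin is given.
- Significance: "A two-sided *p*-value less than 0.05 is considered statistically significant for all tests".
- Missing data: imputed either as success or as failure, without saying which applies when.
- Losses: under Withdrawal, children who move away are left out of the efficacy analysis. Repeated vomiting or a serious adverse event leads to withdrawal. Under the criteria for withdrawal or discontinuation, so does omitting more than one dose.
- Sample size: 72% cure on praziquantel, 5% loss to follow-up, 108 children per arm.

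No sentence makes intention-to-treat the lead for any efficacy outcome.

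**The concern.** Leading with per-protocol can be defended for non-inferiority, because keeping children who did not follow the plan can make two arms look alike and so favour the non-inferiority claim. That argument does not carry over to a test for a difference. There, restricting the analysis to completers gives up the randomised comparison, and if one arm loses its failures that arm looks better than it is.

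Week-12 cure is where a claim that an ACT adds to praziquantel could be made, and the Introduction calls that added benefit unclear. Each of four ACT arms is compared with praziquantel, so there are four opportunities for such a claim.

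The design makes unequal losses possible. The trial is open-label. The criterion of more than one omitted dose can be met on a three-day ACT course but not on a single praziquantel dose.

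**Working it through.** **Inputs from the article.** Control cure is 72%, and there are 108 children per arm. The dropout step reproduces: 102/0.95 = 107.4, rounded up to 108. How the 102 was reached is a separate question and is not used here. Overall loss is 5%. The test is two-sided at 0.05, so the nominal chance of falsely declaring an ACT arm better is 2.5%.

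**Assumptions, not in the article.** True cure among all randomised children is 72% in both arms. A share x of the ACT arm is lost, with cure rate c among those lost. The control arm loses nobody.

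**Formulas.**
- Completers' cure in the ACT arm: p1 = (0.72 − x·c)/(1 − x)
- Apparent benefit: d = p1 − 0.72
- SE = √[p1(1 − p1)/(108(1 − x)) + 0.72 × 0.28/108]
- False-benefit probability = 1 − Φ(1.96 − d/SE)

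**At the planned 5% loss.**
- c = 50%: p1 = (0.72 − 0.025)/0.95 = 0.7316; d = +1.16 points; SE = 6.15 points; 1 − Φ(1.96 − 0.188) = 3.8%. The two-sided error is 5.4%.
- c = 30%: p1 = (0.72 − 0.015)/0.95 = 0.7421; d = +2.21 points; SE = 6.11 points; 1 − Φ(1.96 − 0.362) = 5.5%. The two-sided error is 6.5%.
- c = 72%: p1 = 0.72, d = 0, false benefit 2.5%.

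**At 10% loss in the ACT arm, twice the planned figure.** d = +2.4 points (c = 50%) to +4.7 points (c = 30%), with two-sided error 6.8% to 12.0%.

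**Simulation of the Pearson test** (400,000 runs, 108 per arm), false-benefit rate among completers:
- 5% lost in both arms with the same cure rate among the lost: 2.5% to 2.6%.
- 5% lost in the ACT arm only, cured at half the average rate (36%): 5.0%, apparent benefit +1.9 points.
- 5% lost in the ACT arm only, none cured: 9.2%, +3.8 points.
- 5% lost in the ACT arm only, all cured: 1.4%, −1.5 points.

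If every randomised child's outcome were known, the all-randomised rate would be 2.5% to 2.6% in every scenario.

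**What an all-randomised analysis does when the lost outcomes are missing** (5% loss in the ACT arm only, same normal approximation). Counting missing as failure makes ACT cure 0.72 − 0.05c. Counting missing as success adds 0.05 to that.

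| c | Missing = failure: d, false benefit | Missing = success: d, false benefit |
|---|---|---|
| 50% | −2.5 points, 0.9% | +2.5 points, 6.1% |
| 30% | −1.5 points, 1.4% | +3.5 points, 8.5% |

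The gain therefore depends on naming the missing-outcome rule as well as the set.

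**The case against.** **The losses may not be tied to failure.** Every arm receives the same nurse-observed praziquantel dose on day 0, with one hour of observation and re-dosing after vomiting. If the ACT adds nothing, a child who kept the praziquantel and missed later ACT doses should be cured at about 72%, and the bias is then zero. The set is also defined by completed procedures, not doses taken; non-returners are visited at home, and withdrawn children are sought at week 6. This stands. It is why the point is a risk, and why the 30% to 50% cure among the lost is only an assumption.

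**Intention-to-treat is no cure by itself.** This also stands. With missing counted as success, false benefit is higher than among completers. With missing counted as failure it stays below 2.5% in the scenarios tabulated, but the error shifts against the ACT arm. Nor is that rule safe everywhere: in one simulated case (ACT loses 10%, none cured; control loses 5%, cured at 72%) it gave 8.4% false benefit, against 26.1% among completers. Hence the sensitivity analyses.

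**Scope.** The text next to the lead-set sentence concerns week-6 cure, and the choice of set for secondary outcomes is often left to an analysis plan. But this article does state a choice, in unrestricted terms, and its definition of the set names week 12.

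**A stronger reading.** A reader might infer that the same fault, and the same cure, apply to egg reduction and re-infection. The article does not support that. Re-infection is restricted by definition: "Re-infection rate is the proportion of children who test negative for *S. mansoni* at week 6 but test positive at week 12 follow-up". Egg counts are averaged over non-cured children. Both condition on a post-treatment result, so changing the analysis set alone would not restore the randomised comparison.

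**Conclusion.** The point holds for week-12 cumulative cure. The article extends a per-protocol lead beyond the non-inferiority test that can justify it, to a two-sided difference with no margin. At the planned 5% loss, if it falls on the ACT arm only and 30% to 50% of those lost are cured, the apparent benefit is +1.2 to +2.2 points and the false-benefit error 3.8% to 5.5% instead of 2.5%.

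That is modest, and it rests on losses by arm and cure rates among the lost that the article does not give. Balanced and similar losses, or 72% cure among the lost, give no bias, and better cure among the lost reverses it. A reader might infer that the per-protocol result is bound to favour the ACT arms, or that errors near 12% are to be expected. The article supports neither: the latter needs twice the planned loss, in one arm only, with 30% cure. Intention-to-treat is already planned alongside, which limits the harm but does not settle which result leads.

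**What to change.** State that per-protocol leads only for the week-6 non-inferiority test. For week-12 cure, make the main analysis all randomised children as assigned, using the observed outcome wherever there is one and counting missing outcomes as failure. Report missing counted as success, and per-protocol, as sensitivity analyses. The sentence under Withdrawal that leaves out children who move away needs a matching exception for this analysis.

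The cost is a few sentences. Both analyses are already planned and the sample size does not change. The downside is that counting missing as failure can understate an ACT benefit if the ACT arms lose more children. No change of lead set is asked for egg reduction or re-infection on this ground.
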